**Methods:**

LUSHIP is an Italian multicenter prospective observational study. Patients will be recruited on a nation-wide scale in the 12 participating centers. Patients aged  >  65 years undergoing spinal anesthesia for hip fracture fixation will be enrolled. A lung ultrasound score (LUS) will be generated based on the examination of six areas of each lung and ascribing to each area one of the four recognized aeration patterns—each of which is assigned a subscore of 0, 1, 2, or 3. Thus, the total score will have the potential to range from a minimum of 0 to a maximum of 36. The association between 30-day postoperative complications of cardiac and/or pulmonary origin and the overall mortality will be studied. Considering the fact that cardiac complications in patients undergoing hip surgery occur in approx. 30% of cases, to achieve 80% statistical power, we will need a sample size of 877 patients considering a relative risk of 1.5.

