**Conclusions:**

Lung ultrasound (LU), as a tool within the anesthesiologist’s armamentarium, is becoming increasingly widespread, and its use in the preoperative setting is also starting to become more common. Should the study demonstrate the ability of LU to predict postoperative cardiac and pulmonary complications in hip fracture patients, a randomized clinical trial will be designed with the scope of improving patient outcome.

*Trial registration *ClinicalTrials.gov, NCT04074876. Registered on August 30, 2019.

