Lung ultrasound (LU) has become an indispensable tool within the Anesthesiologist’s diagnostic arsenal, and some reports have started to highlight its role in the perioperative setting for perioperative outcome evaluation [18–20]. It is, therefore, fundamental that the utility of this tool be investigated in a large patient population in much greater detail. Considering the fact that LU examination is based on the exploration of ultrasound artifacts (A-lines, B-lines, lung sliding, focal interstitial syndrome—i.e., multiple B-lines) and the consolidated parenchyma, as well as pleural effusion in patients with pneumonia [21], we hypothesize that this tool may provide better “direct” evidence of preoperative pulmonary status—also supported by the fact that the sensitivity and specificity of LU are both known to be superior to chest radiography, which provides relevant information in just 0.1% of cases [22]. Furthermore, through the detection of diffuse B-lines over different zones, LU permits us to make an “indirect” evaluation of the underlying cardiac status of patients suffering from cardiac disease [23, 24]. Both these characteristics of LU could also echo the American College of Physicians (ACP) recommendation that all patients with hip fracture should undergo a risk assessment that focuses on chronic obstructive pulmonary disease (COPD) and congestive heart failure [25]. The primary aim of the present study is to evaluate, in a large population of elderly patients undergoing hip fracture repair, whether a systematic preoperative LU examination is able to provide bedside real-time information pertaining to the patients’ underlying “indirect” cardiac and “direct” pulmonary statuses, and can be used to asses perioperative cardiac and pulmonary outcome. The second aim is to compare the data gathered in the form of the lung ultrasound score (LUS) with the data provided by the traditional risk scores for preoperative evaluation, i.e., by ASA-PS, RCRI, NSQIP-MICA.

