### Protocol for lung ultrasound

The LUS recognizes four aeration patterns, and assigns to each of them a value ranging between 0 and 3. This evaluation is repeated in six areas of each lung. Using the anterior and posterior axillary line as vertical boundaries, the areas are divided into two anterior (superior and inferior), two lateral, and two posterior areas. The possible patterns are: (i) normal aeration—A-lines or less than two B-lines with lung sliding (score 0); (ii) moderate loss of aeration—three or more well-spaced B-lines with lung sliding (score 1); (iii) severe loss of aeration—coalescent B-lines with lung sliding (score 2); (iv) complete loss of aeration—tissue-like pattern or consolidation (score 3). The sum of all subscores will constitute the overall score. All adjacent intercostal spaces will be analyzed for each area by moving the probe through each space (Fig. 1) and diagram flow (Fig. 2). To standardize the evaluation of LU images, one of the authors ([name]) will coordinate the sharing by e-email of inter-reader agreement video-clip exams between the 12 centers, and the principal investigator for each Institution, plus two collaborators for each center. The ultrasound machine used in the primary center will be the GE Health-Care V-scan, but other machines available in each center could be used. Data collection will continue perioperatively and until hospital discharge for assessment of 30-day clinical deterioration, i.e., pulmonary, MACE, and mortality, defined according to the standards for definitions and use of outcome measures for clinical effectiveness research in perioperative medicine by the European Society of Anesthesia (ESA) and European Society of Intensive Care Medicine (ESICM) [27].

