### Statistical analysis

Continuous normally distributed variables will be presented as means  ±  standard deviations (SD) and compared using the Student’s *t* test. Normality will be assessed using the Shapiro–Wilk test and visual inspection of quantile–quantile plots. Non-normally distributed data will be presented as medians, 1st and 3rd quartiles, and compared using the Wilcoxon rank-sum test. Categorical data will be compared between groups using the *χ*^2^ test, or Fisher’s exact test. Possible correlations between the patient outcomes and changes in LUS score will be examined using the Spearman's rank correlation coefficient. Receiver operating characteristic (ROC) curve analysis will be used to determine optimal cut-off values of LUS score for 30-day clinical deterioration (pulmonary, major cardiovascular events) and mortality. Youden’s index calculation will define the best cut-off value. Cox proportional-hazards models for mortality or clinical deterioration as endpoints allows for the calculation of hazard ratios (HR) of baseline LUS parameters. *P *values less than 0.05 will be considered to indicate statistical significance. Statistical analysis will be performed using the R environment (R Foundation for Statistical Computing, Vienna, Austria) and the appropriate packages.

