## Abbreviations

ASA-PS: American Society of Anesthesiologists Physical Status
ESC: European Society of Cardiology
ESA: European Society of Anesthesiology
RCRI: Revised Cardiac Risk Index
NSQIP-MICA: National Surgical Quality Improvement Program Myocardial Infarction and Cardiac arrest
ACC: American College of Cardiology
AHA: American Heart Association
METS: Metabolic equivalents
BNP: Brain natriuretic peptide
NT-pro-BNP: Pro-natriuretic peptide
NPV: Negative predictive value
ACP: American College of Physicians
COPD: Chronic obstructive pulmonary disease
CEUR-FVG: Ethic Committed of Friuli Venezia Giulia
MACE: Major advance cardiac events
ESICM: European Society of Intensive Care Medicine
GDPR: General data protection regulation
CRF: Case report form
PI: Principal investigator
STARD: Standards for the Reporting of Diagnostic Accuracy Studies
POCUS: Point-of-care ultrasound statement
SD: Standard deviation
ROC: Receiver operating characteristic
HR: Hazard ratios

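### As most naturally read, the ROC and Cox analyses pool pulmonary and cardiac events into one endpoint, which cannot support separate claims of cardiac and of pulmonary prediction

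*Protocol article*

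**What the plan says.** The Statistical analysis section of the protocol article names the endpoints for its two main predictive analyses. ROC curves with Youden's index are to give "optimal cut-off values of LUS score for 30-day clinical deterioration (pulmonary, major cardiovascular events) and mortality". The second analysis is "Cox proportional-hazards models for mortality or clinical deterioration as endpoints", giving hazard ratios for baseline LUS.

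Two other places describe the outcome. The section on the lung ultrasound protocol speaks of "assessment of 30-day clinical deterioration, i.e., pulmonary, MACE, and mortality", and the abstract's Methods of "30-day postoperative complications of cardiac and/or pulmonary origin and the overall mortality". The two Methods sections differ on whether death belongs to clinical deterioration: the ultrasound section includes it, while the Statistical analysis section lists it separately.

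The claims are wider than one combined outcome. The Background separates an indirect cardiac role from a direct pulmonary role and asks whether lung ultrasound "can be used to asses perioperative cardiac and pulmonary outcome". The abstract's conclusion makes the design of a later randomised trial conditional: "Should the study demonstrate the ability of LU to predict postoperative cardiac and pulmonary complications in hip fracture patients". The Discussion repeats that condition. The Power analysis rests on MACE alone (rate about 30%, relative risk 1.5, 877 patients, 80% power).

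**The concern.** An endpoint met by a pulmonary **or** a cardiac event cannot show that a score predicts pulmonary **and** cardiac events. LUS images the lung directly, so an association with pulmonary complications is the more immediate of the two hypotheses. The cardiac link is the indirect one and most needs its own test. If LUS were related only to pulmonary events, the pooled hazard ratio or AUC could still be clearly positive and be reported in the article's own terms as cardiac and pulmonary prediction. The mirror case is equally possible: a purely cardiac association could be read as pulmonary prediction too.

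The mismatch is internal to the article. MACE is the outcome on which the study was sized, yet no ROC or Cox analysis is stated for it alone. Adding detail to the definition of clinical deterioration would not cure this while the two event types stay merged.

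**Working it through.** **Inputs from the article.** Power analysis: 877 patients; 40% with altered LUS, unexposed/exposed ratio 1.5, so 526 unexposed and 351 exposed; MACE 30%; relative risk 1.5. Statistical analysis: significance level 0.05, sidedness not stated.

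**Assumptions.** Two-sided test; pulmonary rate P from 5% to 20% overall; pulmonary relative risk R from 1.5 to 3; the two event types independent, with a check on that below. A comparison of two proportions stands in for the Cox test.

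**The plan's own figure.** Take 30% MACE overall with relative risk 1.5, so 25% v 37.5%. The usual formula for the unexposed group is [1.96·√(2.5·p̄(1−p̄)) + 0.8416·√(p0(1−p0) + 1.5·p1(1−p1))]² / (p1−p0)². With p̄ = 0.30 this is (1.420 + 0.618)² / 0.0156 = 266 unexposed, plus 178 exposed, 444 in total. Reading 30% as the unexposed rate gives 337, and as the exposed rate 605. The stated 877 is not reproduced. That is a separate matter; here 877 is used as planned.

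**Chance of a significant pooled result when LUS is unrelated to MACE.**
1. Pulmonary risk: p0 = P / (0.6 + 0.4R) in the unexposed, p1 = R·p0 in the exposed.
2. Pooled risk: a = 1 − 0.70(1 − p0) and b = 1 − 0.70(1 − p1).
3. Power = Φ{(b − a − 1.96·s0)/s1}, with s0 = √(p̄(1−p̄)(1/526 + 1/351)), p̄ the pooled risk over both groups, and s1 = √(a(1−a)/526 + b(1−b)/351).

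Example, P = 15% and R = 2: p0 = 0.15/1.4 = 0.107 and p1 = 0.214; a = 0.375, b = 0.450, ratio 1.20; s0 = 0.0338, s1 = 0.0339; (0.075 − 0.0663)/0.0339 = 0.256; power 60%.

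| Pulmonary rate | R = 1.5 | R = 2 | R = 3 |
|---|---|---|---|
| 5% | 7% | 12% | 22% |
| 10% | 14% | 32% | 65% |
| 15% | 25% | 60% | 93% |
| 20% | 40% | 83% | 99.5% |

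If 15% is taken as the rate in the unexposed instead of overall, the pooled risks at R = 2 are 40.5% v 51.0% and the 60% becomes 87%.

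**Overlap of event types.** If a share f of pulmonary events falls in patients who also have MACE, the pooled risk is 0.30 + (1 − f)p. Independence is f = 0.30. At P = 15%, R = 2:
- f = 0.50: 35.4% v 40.7%, power 36%
- f = 0.70: 33.2% v 36.4%, power about 16%

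**The mirror case.** LUS related only to MACE, 25% v 37.5%: power is 98% on MACE alone. Adding independent, unrelated pulmonary events at 10%, 15% and 20% gives pooled risks of 32.5% v 43.8%, 36.3% v 46.9% and 40% v 50%, with power 92%, 88% and 83%.

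**Can MACE be analysed alone?** At 877 patients and relative risk 1.5, power is 99.5%, 98% or 92% with 30% read as the unexposed, overall or exposed rate. With the level halved to 0.025 for two endpoints it is 98.9%, 95.5% or 87.1%.

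**The case against.** **Pooling is inferred.** The article never calls the outcome composite or combined. It plans cut-off values in the plural, and the parenthesis in the ROC sentence could be a list of separate outcomes. Clinical deterioration includes death in one section but not in the other, so the label may partly be a heading. This stands to the extent that pooling must be called the natural reading and not a certainty. Against the list reading, the Cox sentence uses clinical deterioration as one endpoint set against mortality, and the abstract joins the two origins with and/or.

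**Component analyses may be in the analysis plan.** They may, and the χ² comparisons in the article could be applied to MACE. Silence on components would not be a finding. The point is that the endpoint the article does name for ROC and Cox does not match the conclusion it announces.

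**The size depends on assumptions.** This stands. The only relative risk in the article is 1.5, stated for MACE; at that value for pulmonary events the chance is 7–40% across the rates tried, and overlap lowers it further.

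**Stronger readings that the article does not support.** A reader might infer that the second aim, to "compare the data gathered in the form of the lung ultrasound score (LUS) with the data provided by the traditional risk scores", would be biased in favour of LUS because RCRI and NSQIP-MICA are cardiac scores judged on a pooled endpoint. No section says which endpoint that comparison uses. A reader might also infer that unrelated pulmonary events would leave the study underpowered for a cardiac effect. On the stated relative risk, power stays at 83–92%, above the planned 80%. Nor would a positive result by itself start a randomised trial; the abstract says that one will be designed.

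**Conclusion.** The concern holds on the natural reading of the Statistical analysis section: one pooled endpoint for ROC and Cox, set against a two-part claim and a sample size built on MACE. A significant pooled result would not show which part of the claim is true. With no cardiac association at all, the chance of such a result runs from 7% to 99.5% over pulmonary rates of 5–20% and relative risks of 1.5–3. It is small when pulmonary events are rare or weakly related to LUS, and high when they are common and strongly related. These figures rest on an assumed pulmonary rate, independent event types and a two-sided 0.05 test.

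The data would remain usable, so this is a change that should be made and not a fatal flaw. If separate analyses were always intended, the text still needs to say so.

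**What to change.** In the Statistical analysis section, state that the ROC and Cox analyses are run separately for MACE and for pulmonary complications, counting the first event of each type and not letting one type censor the other. Keep the pooled endpoint as supportive. State that a conclusion about cardiac complications rests on the MACE analysis only, and one about pulmonary complications on the pulmonary analysis only. In the same edit, reconcile whether death is part of clinical deterioration.

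The cost is a few sentences and some extra model runs; the article already lists pulmonary events, MACE and mortality as separate items to be assessed, so no further patients or procedures are needed. Each analysis has fewer events than the pooled one: about 0.30 × 877 = 263 MACE, and between 44 and 175 pulmonary events at assumed rates of 5% to 20%. Intervals will be wider and two results must be reported. On the article's own inputs the MACE analysis keeps at least 87% power, even with the level halved.

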### Power analysis

We estimate that 40% of patients have focal or diffuse B-lines with an altered LUS score—unexposed/exposed ratio: 1.5—and that 30% of patients have no B-lines, but could run into MACE with a relative risk of 1.5 [30, 31]. Considering that the rate of MACE in patients undergoing hip surgery is about 30%, we calculated a relative risk of 1.5. Therefore, we estimated that we would need a sample size of 877 patients in order to obtain 80% statistical power.

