More and more anesthesiologists are turning to LU [35]. Some studies reveal LU to have higher diagnostic accuracy than chest X-rays in the perioperative setting for the direct assessment of the most frequent lung diseases, such as pleural effusion, consolidation, and interstitial syndrome [20, 36]. Another recent study in vascular surgery patients (the LUPPO study) indicated that LU could help evaluate “indirect” cardiac status at the bedside [19]. This is because B-lines tightly correlate with interstitial lung syndrome of cardiac origin [37]. On the contrary, the absence of multiple B-lines excludes pulmonary edema with a high negative predictive value [24, 38]. Furthermore, an expert consensus document reporting a checklist for the quantification of pulmonary congestion by LU in heart failure reports that LU can provide useful information [24]. Considering the above, we designed this multicenter observational study to assess the utility of LU in the management of frail elderly patients undergoing hip fracture repair.

Our study protocol has some limitations: first of all, the different participating centers may have different levels of experience in LU use and may operate different ultrasound machines for LU evaluation; second, distinct perioperative clinical management in different centers could influence patient clinical course and the incidence of complications. However, if we demonstrate LU to have the ability to predict postoperative cardiac and pulmonary complications in hip fracture patients, our observational study will help pave the way to the generation of future hypotheses and the design of further randomized clinical trials directed at improving patient outcome. To say that we acknowledge as a study limitation that patients with known acute heart failure or MACE at “priori” were excluded to have a pure vision about LU prediction.

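### The protocol names possible centre effects on both the lung ultrasound score and complications, but none of its listed analyses includes centre

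*Protocol article*

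**What the plan says.** **Analysis.** Statistical analysis lists t, Wilcoxon rank-sum and chi-square or Fisher tests, Spearman correlation, ROC curves with a Youden cut-off, and Cox models for mortality or clinical deterioration. The use of Cox models, it says, "allows for the calculation of hazard ratios (HR) of baseline LUS parameters". No centre stratum, centre term or random effect is named. Power analysis does not mention centre either.

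**Centre and the exposure.** The limitations paragraph of the Discussion says that "the different participating centers may have different levels of experience in LU use and may operate different ultrasound machines for LU evaluation". Protocol for lung ultrasound names one device for the coordinating site and lets other sites use their own.

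**Centre and the outcome.** The same paragraph says that "distinct perioperative clinical management in different centers could influence patient clinical course and the incidence of complications".

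**Safeguards in the design.** The scoring rule is fixed, video clips are exchanged among all 12 centres to check reader agreement, and outcomes follow a published European standard (all in Protocol for lung ultrasound). Every site uses the same case report form, and two independent investigators check the database (Patient consent and data protection).

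**The concern.** A factor that can shift both the recorded LUS and the recorded events is a potential confounder of their association. The protocol supplies both halves: skill and machine on the LUS side, management on the event side. It then treats the matter as a limitation to disclose, although the between-centre part can be handled in the analysis.

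Suppose some sites record more B-lines and also have more complications, for reasons unrelated to the individual patient's lungs. The pooled data then show LUS associated with outcome even if it predicts nothing within any site. With the reverse pattern, a real association is diluted. A pooled Youden cut-off is also hard to interpret if the same lung would score differently at two sites.

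The Conclusions of the Abstract make a randomised trial depend on showing that ultrasound predicts complications. A between-centre artefact could therefore feed into that decision.

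**Working it through.** **Inputs from the documents**
- Significance level: P "values less than 0.05 will be considered to indicate statistical significance". Sidedness is not stated; two-sided is assumed.
- Size: "we would need a sample size of 877 patients in order to obtain 80% statistical power".
- Exposure: "We estimate that 40% of patients have focal or diffuse B-lines with an altered LUS score", with "unexposed/exposed ratio: 1.5".
- Event rate about 30%, relative risk 1.5 (Power analysis); 12 centres (Study design and patients).

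**Inputs that are assumptions.** The between-centre SDs (logit scale), their correlation and near-equal recruitment (11 × 73 + 74 = 877) are not in the documents. To give a feel for the SDs, take logit(0.30) = −0.847. One SD of 0.5 either side gives centre event rates of about 21% and 41%; an SD of 0.3 gives 24% and 37%. For LUS, logit(0.40) = −0.405. An SD of 0.5 gives altered-LUS rates of 29% and 52%, and 0.8 gives 23% and 60%.

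**The plan's own figure.** Take 45% against 30%, a 1.5:1 ratio, two-sided 5% and 80% power. The pooled rate is (0.45 + 1.5 × 0.30)/2.5 = 0.36, and the exposed group needs

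[1.96·√(1.667 × 0.36 × 0.64) + 0.842·√(0.45 × 0.55 + 0.30 × 0.70/1.5)]² / 0.15² = 134.3, so 135.

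The total is 135 × 2.5 ≈ 338, not 877. Reading 1.5 as an odds ratio (30% against 39.1%) gives 883, which is close. The centre question does not depend on how this is settled, so 877 is used as stated.

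**Mechanism by hand.** Let half the patients be at sites with 50% altered LUS and 36% events, and half at sites with 30% and 24%. Within each site LUS and events are independent.
- Exposed: (0.5 × 0.36 + 0.3 × 0.24)/0.8 = 0.315
- Unexposed: (0.5 × 0.36 + 0.7 × 0.24)/1.2 = 0.290
- Pooled relative risk: 0.315/0.290 = 1.09, significant in about 12% of studies of 877 rather than 5%.

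Swap the event rates and the pooled relative risk is 0.285/0.310 = 0.92, again significant in about 12%, now in the wrong direction.

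**Simulation.** There is no within-centre association, average altered LUS is 40% and average events 30%. The pooled chi-square test is compared with a Mantel-Haenszel test stratified by centre. Figures are from 4,000 runs per setting; those in brackets are from a separate simulation with 1,500 runs.

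| SD LUS / events | Correlation | Pooled type I error | Stratified | Median pooled RR |
|---|---|---|---|---|
| 0 / 0 | 0 | 5.1% | 5.2% | 1.00 |
| 0.3 / 0.3 | 0 | 5.3% | 5.0% | 1.00 |
| 0.3 / 0.3 | 0.5 | 5.6% | 4.4% | 1.03 |
| 0.3 / 0.3 | 0.8 | 7.5% | 4.9% | 1.04 |
| 0.5 / 0.5 | −0.5 | 12.1% | 4.6% | 0.93 |
| 0.5 / 0.5 | 0 | 6.7% (7.5%) | 5.3% (5.3%) | 1.00 |
| 0.5 / 0.5 | 0.5 | 13.2% (14.2%) | 5.2% (3.8%) | 1.08 |
| 0.5 / 0.5 | 0.8 | 22.6% (22.4%) | 5.3% (4.5%) | 1.12 |
| 0.8 / 0.5 | 0 | 9.4% (11.3%) | 5.0% (5.3%) | 1.00 |
| 0.8 / 0.5 | 0.5 | 22.8% (20.7%) | 4.3% (4.7%) | 1.11 |
| 0.8 / 0.5 | 0.8 | 37.2% (39.9%) | 4.9% (5.1%) | 1.18 |

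Independent centre effects still inflate the error because 12 centres align by chance: the sampling SD of a zero correlation is about 1/√11 = 0.30. The simulation covers a binary comparison. Cox models and the AUC were not simulated; the same mechanism applies to them, but the percentages need not carry over exactly.

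**The case against.** **Silence is not a plan to ignore centre.** A reader might infer that the protocol says its centres do differ and that every analysis will disregard this. The text supports neither. The limitations say *may* and *could*. The Cox sentence names LUS but does not say that LUS is the only term, and a fuller protocol or SAP could add centre. This stands, and it limits the point to what the listed analyses contain. It does not remove the point: the t, Wilcoxon, chi-square, Spearman and ROC analyses, as named, are ordinary patient-level methods without strata, and they sit beside a threat that the authors themselves identify.

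**The design already standardises.** The clip exchange, common form and published outcome definitions should shrink centre differences in reading and recording. That also stands. They do not reach machine, image acquisition or local management.

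**The size is assumed.** The documents give no between-centre variation and no reason why reading differences should line up with management differences. The largest figures need strong alignment, and the spurious relative risks of 1.08–1.11 at correlation 0.5 are small beside the planned 1.5. All of this is correct.

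**Pooled discrimination is a legitimate target.** The study is framed as diagnostic accuracy, and if case mix differs by site, conditioning on centre removes some genuine prognostic information. This is a reason to report both analyses, not the pooled one alone.

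**Conclusion.** The point holds in a limited form. The protocol acknowledges possible centre influences on LUS and on complications, and none of its listed analyses includes centre. Followed as written, the plan leaves a confounder of its own naming uncontrolled.

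The consequence is conditional. With moderate centre effects (logit SD 0.5–0.8 for LUS, 0.5 for events), pooled type I error is about 7–11% without alignment and 13–23% at correlation 0.5, against about 4–5% when stratified. With small effects (SD 0.3) it is 5–6% for correlations of 0 and 0.5, and 7.5% at 0.8. Opposite alignment pushes the estimate the other way and can hide a real association. Every SD and correlation here is an assumption, as is near-equal recruitment.

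The documents do not show that a spurious association will occur, nor that centre will certainly be omitted. The change should be made because the threat is self-identified and the remedy is inexpensive.

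**What to change.** - **Cox models:** stratify by centre, or use a centre frailty term if events per centre are few.
- **Binary comparison of LUS with outcome:** use a Mantel-Haenszel analysis stratified by centre, or a logistic model with a random centre intercept, in place of the plain chi-square test.
- **ROC analysis:** report an AUC formed from pairs within the same centre beside the pooled AUC and cut-off.
- **Keep the pooled results** and present the two sets together, so that a gap between them is visible.

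**Cost.** No new data are needed, since each site's investigator uploads that site's records. Some precision is lost, roughly the share of LUS variation that lies between centres. To first order this is (SD × 0.24)²/0.24, where 0.24 = 0.40 × 0.60: 0.0144/0.24 = 6% at SD 0.5 and 0.0369/0.24 = 15% at SD 0.8. Standard errors would be about 3% and 9% larger (1/√0.94 and 1/√0.846). The loss is greater if recruitment is uneven or deaths per centre are few; the documents give neither. Centre adjustment may also remove real case-mix information, and it cannot correct reader differences within a centre.
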